### Statistical analysis plan

#### Overall principles

Analysis will start once all data for the last included participant have been obtained, the database has been cleaned and locked, and the study protocol has been submitted for publication. All analyses will be carried out using the R statistical software (R Development Core Team–version to be determined at time of analysis) [17]. Estimate effects will be reported with 95% CIs. A significance level of 0.05 will be used for all statistical comparisons. Secondary analyses and subgroup analyses will not be adjusted for multiple comparisons. They should, therefore, be interpreted as exploratory.

#### Handling missing data

No data imputation will be performed for main exposure (vaccination status) and for the study outcome. Main analysis will consist of observed data, without imputation. For sensitivity analysis we will perform multiple imputation if missing data on core variables is > 5%, under the assumption that the missingness pattern is missing at random conditional on the observed data. Core variables are defined as the covariates to be used in the primary analysis: age, gender, Charlson comorbidity index [18], current smoking status, and body mass index (BMI) category.

#### Participant flow

The flow of participants will be displayed in accordance with the Strengthening the Reporting of Observational Studies in Epidemiology (STROBE) flow diagram (STROBE 2007 statement) [19]. This description will include information about the number of screened for enrollment, reasons for non-participation, number of actually enrolled, and number of analyzed.

#### Baseline characteristics

The baseline characteristics of participants will be presented for the entire study population, test-positive cases, and test-negative controls. Categorical variables will be described as absolute and relative frequencies. Continuous variables will be expressed as mean (standard deviation) for variables with symmetric distribution, and as median (interquartile range) for variables with asymmetric distribution. The symmetry of continuous variables will be checked using graphical analysis of histograms and by the Shapiro-Wilk test.

#### Primary outcome analysis

The primary study analysis compares the vaccine effectiveness for symptomatic SARS-CoV-2 infection of participants vaccinated with two or more doses of BNT162b2 mRNA and participants never vaccinated. Logistic regression adjusted by age, gender, Charlson comorbidity index, BMI, and current smoking status will be used to estimate the odds ratio of vaccination among test positive cases and test negative controls. We also will incorporate in the model the time (number of days) elapsed between the study start and date of RT-PCR sample collection as a proxy of temporal trend. The reference group for vaccination status will be those who had not received a first vaccine dose before the date of sample collection. The estimate of vaccine effectiveness will be provided by 1 –odds ratio x 100 under the assumptions of a test negative design [20]. 95% CIs will be calculated using the Wald method.

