#### Sensitivity analyses for the primary outcome

The following sensitivity analyses will be conducted to assess consistency and risk of bias: (1) performing multiple imputation for missing core variables data (see *handling missing data section*); (2) considering only the first enrollment of each individual for the study; (3) excluding as controls those with less than 5 days of symptom onset.

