#### Secondary outcome analyses

The association between the exposition variables with symptomatic SARS-CoV-2 infection caused by circulating variants as well as the association between secondary exposition variables with symptomatic SARS-CoV-2 infection will be assessed using the same statistical model used for the primary outcome.

Crude and adjusted generalized linear models will be used to assess the impact of exposures on duration of COVID-19 symptoms, hospitalisation for COVID-19, need for ICU admission, need for invasive mechanical ventilation, death from COVID-19, health-related quality of life, persistent COVID-19 symptoms, symptomatic SARS-CoV-2 reinfection among participants with a positive RT-PCR result for SARS-CoV-2, and to test associations between length of time after receipt of the second or third dose of BNT162b2 and the risk of symptomatic SARS-CoV-2 infection, according to the probability distribution of each outcome. Quantitative outcomes will be expressed as mean difference. Categorical outcomes will be expressed as hazard ratio or relative risk as appropriate.

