## Study status

The study design and protocol were finalised in October 2021. The first participant was included on November 3, 2021. At study start, approximately 2/3 of the target population was fully vaccinated. Two thousand and thirty-four participants were enrolled up to February 2, 2022. Currently, this study is recruiting participants in 3 referral COVID-19 sites in Toledo. We anticipate that the recruitment will be completed in July 2022.

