### Protocol review and amendments

#### Sample size review

According to the original sample size estimation, 2,979 participants (993 cases and 1,986 controls) would be required to detect an odds ratio ≤ 0.70 for the primary outcome analysis, assuming the recruitment of two controls per case, a rate of complete vaccination with the Pfizer-BioNTech BNT162b2 mRNA vaccine of 60% in the control group, a two-tailed alpha of 5%, a power of 80%, and an increased sample size by 30% (due to parameter uncertainties and need for covariate adjustment). In order to achieve adequate power to assess the impact of BNT162b2 on symptomatic SARS-CoV-2 infection associated with the Gamma variant (predominant SARS-COV-2 lineage at the time of study protocol development), considering a rate of 32.5% of genotyping tests with inconclusive results and a prevalence of 90% of the Gamma variant, the original sample size was determined to be 4,500 participants (1,500 cases and 3,000 controls).

In January 2022, the study sample size was revised, given the frequent variation of COVID-19 pandemic factors that could impact sample size estimation (e.g., emergence of Omicron variant, scarcity of new COVID-19 cases due to Gamma variant, increase in vaccine coverage, and vaccine effectiveness variations for distinct SARS-CoV-2 variants). Revision was made based solely on the number of recruited patients, number of cases and proportion of positive cases in the whole sample, without any additional analysis. The original study sample size (4,500 participants) was judged to provide an appropriate power to assess the primary outcome analysis as described in the sample size section.

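### Calendar time enters the primary model as a day count, read most plainly as one linear term; this may leave residual time confounding of unknown size, and a flexible term is a cheap improvement

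*Protocol article*

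**What the plan says.** The Primary outcome analysis section describes an unconditional model: "Logistic regression adjusted by age, gender, Charlson comorbidity index, BMI, and current smoking status will be used to estimate the odds ratio". Calendar time is then added as "the time (number of days) elapsed between the study start and date of RT-PCR sample collection as a proxy of temporal trend". No spline, calendar category, date matching or conditioning on date is mentioned.

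The Sensitivity analyses section lists three items: multiple imputation, "considering only the first enrollment of each individual for the study", and dropping controls with fewer than 5 days since symptom onset. None changes the handling of time.

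For the circulating variants, the Secondary outcome analyses section says that associations "will be assessed using the same statistical model used for the primary outcome". It does not say which control dates enter each variant analysis.

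On the period covered, Study status says "The first participant was included on November 3, 2021" and "We anticipate that the recruitment will be completed in July 2022". The Sample size review gives as reasons for revisiting the assumptions "emergence of Omicron variant, scarcity of new COVID-19 cases due to Gamma variant, increase in vaccine coverage, and vaccine effectiveness variations" for distinct variants. In the Discussion, the limitations paragraph relies on adjustment for time-related as well as personal variables to reduce confounding.

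**The concern.** In a test-negative study, calendar time can drive both the chance of testing positive (through epidemic waves) and the chance of being vaccinated (through the campaign). It is therefore a natural confounder here, and the plan rightly includes it. The question is the form.

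A day count put into a logistic model as it stands forces the log-odds of a positive test to follow one straight line for about nine months. Such a line cannot follow a rise and fall in positivity. If unvaccinated people are relatively more common before a wave and vaccinated people during it, the line leaves part of that imbalance in the odds ratio and VE is understated. The error does not shrink with sample size, and the Wald interval does not show it.

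The variant-specific analyses reuse the same model. If controls sampled before a variant appeared stay in the comparison, the outcome's dependence on date is even further from a straight line.

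**Working it through.** **1. The plan's own precision figure.** The Sample size section gives VE 80% (OR 0.20), 90% coverage in controls, two controls per case and a precision width of 10%.

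- Exposure in cases: p1 = 0.9×0.2 / (0.1 + 0.9×0.2) = 0.643.
- Half-width on the log scale for a full VE interval of 10 points: d = asinh(0.10 / (2×0.20)) = 0.2475.
- Cases: 1.96² × [1/(p1(1−p1)) + 1/(2×0.9×0.1)] / d² = 3.84 × (4.356 + 5.556) / 0.0612 = 621.7, so 622. This matches the stated figure.
- Implied 95% CI at VE 80%: 74.4% to 84.4%. This is the yardstick for any bias.

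**2. Time span.** Day 0 is 3 November 2021. On enrolment, the article says "Two thousand and thirty-four participants were enrolled up to February 2, 2022". That is day 91, and 2,034/4,500 = 45% of the target. July 2022 is about day 240 to 270.

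**3. Large-sample limit of the linear-day model.** The documents give no positivity or coverage by date, so every curve here is an assumption. The true OR is constant over 270 days, with 2,034 enrolled by day 91 and the other 2,466 afterwards. For each curve the model logit P(case) = a + b·vaccinated + c·day was fitted to the expected cell counts, with VE = 1 − exp(b). The same was done with 14-day categories in place of c·day.

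- Positivity odds in the unvaccinated, four curves: one wave peaking at day 85 (10% to 65%); that wave plus a smaller one at day 235; a steep wave at day 85 (3% to 75%); a late wave at day 200.
- Coverage among controls, 13 curves: flat at 0.90; or starting at 0.50, 0.67 or 0.80 and rising to 0.92–0.93, either on a straight logit line or saturating with a time constant of 30, 60 or 120 days.

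VE (%) from the linear-day model, coverage starting at 0.67; each cell is true 80% / true 50%:

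| Coverage path | One wave, day 85 | Two waves | Steep wave, day 85 | Late wave |
|---|---|---|---|---|
| straight on logit scale | 80.0 / 48.9 | 80.0 / 49.6 | 80.1 / 48.5 | 79.8 / 48.9 |
| saturating, 120 days | 79.2 / 47.1 | 79.7 / 48.8 | 78.9 / 45.9 | 79.7 / 49.0 |
| saturating, 60 days | 77.2 / 41.7 | 78.6 / 45.9 | 75.9 / 37.5 | 79.5 / 48.9 |
| saturating, 30 days | 74.6 / 35.5 | 77.0 / 42.3 | 71.8 / 27.3 | 80.0 / 50.2 |

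Over all 4 × 13 = 52 combinations:

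- True VE 80%: linear day 67.6% to 80.8%; median absolute bias 0.6 points; 75% of combinations within 2 points and 90% within 5. Fortnight categories gave 79.8% to 80.0%.
- True VE 50%: linear day 14.0% to 50.2%; median absolute bias 1.6 points; 71% within 5 points. Fortnight categories gave 49.5% to 50.0%.
- Flat or logit-straight coverage: bias under 1 point at VE 80% and under 2 points at VE 50%, whatever the wave.
- The lowest values (67.6% and 14.0%) come from coverage rising from 0.50 to 0.92 with a 30-day constant just before the steep wave.

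**4. Does the day term still help?** It depends on the curve. With the late wave and logit-straight coverage from 0.67, it moves the estimate from 70.1% (no time term) to 79.8%. With one wave at day 85 and the 30-day rise from 0.67, it moves it from 77.3% to 74.6%, further from the true 80%.

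**5. Variant-specific VE.** Assume variant cases only from day 45, all controls kept, one wave (10% to 70%, peak near day 80), and coverage 0.67 to 0.92 with a 30–60 day constant. The linear-day model returned 73–75% for a true 80% and 32–36% for a true 50%. With no time term the figures were 75–77% and 38–43%. Fortnight strata were within about 0.2 points of the truth.

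**The case against.** The strongest reply is that the article names a variable and its unit, not a functional form. Days since start is also the input to a spline. Age and BMI appear in the same sentence without a form, although the missing-data section shows that BMI is used in categories. Form is commonly left to an analysis plan, and none is shown. This stands in part: linear is the plain reading, not a stated fact.

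Second, waves in positivity are not enough to create bias. Coverage must also depart from a straight trend in step with them. This stands. A separate two-wave check (days 90 and 240) with straight-line coverage, 80% to 94% or 60% to 95%, returned 80.0–80.2% for a true 80% and 50.0–50.1% for a true 50%.

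Third, the article does not measure how coverage moved within the analysis set. The two-thirds in Study status refers to full vaccination in the target population; the 90% in the Sample size section refers to controls. The denominators differ, so the pair cannot be read as a rise from 67% to 90%. A second wave late in recruitment is likewise an assumption. This stands.

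A reader might therefore infer that the plan commits to a straight line and that the primary VE is seriously biased. The documents support neither as a certainty. A reader might also infer that pre-Omicron controls are certain to be used in the Omicron analysis. The article only says that the model is the same, and it labels secondary analyses exploratory.

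What remains is that the article states the unit and role of the time term, gives no sign of a flexible form, and tests no alternative.

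**Conclusion.** The point holds as a cheap improvement that should be made, not as a demonstrated error. If time enters as one linear term, residual confounding is possible and its size is unknown.

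Under the assumed curves, and with VE constant over time, the bias at a true VE of 80% is below 1 point when coverage is flat or logit-straight. It is about 1 to 6 points downward in most cases where coverage rises quickly and saturates around a wave, and up to about 12 points at the extreme (80 − 67.6 = 12.4). At a true VE of 50% it is larger, up to 36 points in the same extreme case (50 − 14.0). Against a planned interval of 74.4% to 84.4%, a shift of 5 points would use up the whole half-width.

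The largest figures are corner cases and should not be quoted as expected bias. The sponsor could not know in advance which case would apply, and the fortnight term was within 0.5 points of the truth in every combination of the grid.

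**What to change.** State the form of the time term before database lock. In the primary model, use a natural or restricted cubic spline of sampling date with knots fixed in advance, or calendar-fortnight (or week) categories. Keep the linear-day model as a sensitivity analysis, so that the effect of the choice is visible.

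For variant-specific VE, use the same flexible term and restrict controls to sampling dates between the first and last local detection of that variant.

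The cost is small. Sampling date is already in the model. A spline takes a few degrees of freedom. Fortnight categories over 270 days take about 19 (270/14 = 19.3, so 20 categories). With about half of enrolment eligible for the primary analysis, as the Sample size section assumes, there would be about 750 cases and 1,500 controls to support either. Weekly categories (270/7, about 39) could be thin in quiet weeks, which favours the spline or fortnights. The variant analyses would lose some controls.

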#### Sensitivity analyses for the primary outcome

The following sensitivity analyses will be conducted to assess consistency and risk of bias: (1) performing multiple imputation for missing core variables data (see *handling missing data section*); (2) considering only the first enrollment of each individual for the study; (3) excluding as controls those with less than 5 days of symptom onset.

#### Subgroup analyses for the primary outcome

Subgroup analyses, by means of interaction tests, will be conducted to explore potential differences in vaccine effectiveness for symptomatic SARS-CoV-2 infection by age group (12–17, 18–64, and ≥ 65 years), BMI categories, cardiovascular disease (composite of heart failure, ischemic heart disease, cerebrovascular disease, and peripheral arterial disease), and Charlson Comorbidity index ≥ 2.

#### Secondary outcome analyses

The association between the exposition variables with symptomatic SARS-CoV-2 infection caused by circulating variants as well as the association between secondary exposition variables with symptomatic SARS-CoV-2 infection will be assessed using the same statistical model used for the primary outcome.

Crude and adjusted generalized linear models will be used to assess the impact of exposures on duration of COVID-19 symptoms, hospitalisation for COVID-19, need for ICU admission, need for invasive mechanical ventilation, death from COVID-19, health-related quality of life, persistent COVID-19 symptoms, symptomatic SARS-CoV-2 reinfection among participants with a positive RT-PCR result for SARS-CoV-2, and to test associations between length of time after receipt of the second or third dose of BNT162b2 and the risk of symptomatic SARS-CoV-2 infection, according to the probability distribution of each outcome. Quantitative outcomes will be expressed as mean difference. Categorical outcomes will be expressed as hazard ratio or relative risk as appropriate.

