### Outcomes

The primary outcome is symptomatic COVID-19, defined by the presence of at least one COVID-19-like symptom as listed in Participants section and confirmed by a positive RT-PCR result for SARS-CoV-2 infection from participants’ NP or nasal swabs.

Secondary outcomes are: (1) symptomatic SARS-CoV-2 infection associated with circulating variants (e.g., Delta, and Omicron); (2) duration of COVID-19 symptoms; (3) hospitalization for COVID-19 within 30 days from enrollment among patients with confirmed COVD-19; (4) need for ICU admission within 30 days from enrollment among patients with confirmed COVD-19; (5) need for invasive mechanical ventilation within 30 days from enrollment among patients with confirmed COVD-19; (6) death from COVID-19 within 90 days from enrollment among patients with confirmed COVD-19; (7) health-related quality of life at 90 days from enrollment among patients with confirmed COVD-19, measured by the three-level version of the EuroQol five-dimensional descriptive system (range, -0.17 [worst] to 1.0 [best]; minimal important difference, 0.03) [7, 8]; (8) persistent COVID-19 symptoms at 180 days from enrollment among patients with confirmed COVD-19; (9) symptomatic SARS-CoV-2 reinfection within 365 days from enrollment among patients with confirmed COVD-19, defined as recurrence of COVID-19-like symptoms confirmed by a positive RT-PCR or antigen test for SARS-CoV-2 more than 90 days after primary infection.

Safety data including adverse events and serious adverse events will be assessed upon inclusion of cases and controls and over the 12-month follow-up for cases, under the standard of care procedures for the city of Toledo’s surveillance program per Brazilian regulatory authority’s requirements.

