### Sample size

The sample size was calculated based on formulas published by O’Neill RT [9]. Assuming the recruitment of two controls per case, a vaccine coverage rate of 90% among controls, a sample of 622 cases and 1,244 controls will be required to detect a vaccine effectiveness of 80% with a precision width of 10%. Considering that around 50% of enrolled participants will fulfil criteria for the primary analysis (≥ 2 doses of BNT162b2 or unvaccinated) and increasing the sample size by 20% (due to parameter uncertainties, potential COVID-19 misclassifications, and need for covariate adjustment), the study will need to include 1,500 cases and 3,000 controls.

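### Variant-specific effectiveness combines an unrestricted control set with a single day-count term of unstated form, which can bias Omicron effectiveness downward if that term is linear and coverage rose early then levelled off

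*Protocol article*

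**What the plan says.** *Secondary outcome analyses* states that variant-specific infection "will be assessed using the same statistical model used for the primary outcome". *Primary outcome analysis* defines that model: "Logistic regression adjusted by age, gender, Charlson comorbidity index, BMI, and current smoking status will be used" to compare test-positive cases with test-negative controls, and "We also will incorporate in the model the time (number of days) elapsed between the study start and date of RT-PCR sample collection" serves "as a proxy of temporal trend". The article does not say whether this day count is linear, a spline or categorical. Neither section ties the controls of a variant analysis to the dates on which that variant was circulating.

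Three other places bear on the point. *Sample size review* lists, among the factors that prompted the January 2022 revision, "emergence of Omicron variant, scarcity of new COVID-19 cases due to Gamma variant, increase in vaccine coverage". *Study status* reports "At study start, approximately 2/3 of the target population was fully vaccinated", with the first inclusion on 3 November 2021 and recruitment expected to end in July 2022. *Sample size* plans on "a vaccine coverage rate of 90% among controls".

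**The concern.** In a test-negative design the controls show how common vaccination was in the population from which the cases arose. In the all-variant primary analysis every recruitment week can yield a case. In an Omicron analysis the weeks before Omicron can yield only controls. If coverage was lower in those weeks, vaccination looks rarer among controls than it was while Omicron circulated. The odds ratio moves up and Omicron VE moves down, unless the time term absorbs the difference.

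One straight-line day count may not absorb it, because the log-odds of being an Omicron case rather than a control do not follow a line. They are undefined (zero cases) at first and then jump. At stake is the first secondary objective, and the Discussion presents variant-specific effectiveness as a strength of the study. A downward shift in Omicron VE with Delta VE nearly unchanged would also make the Delta-Omicron contrast look larger than it is.

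**Working it through.** **Plan's own figure.** The article does not size the variant analyses under the current plan. The one figure that uses the 90% coverage input is the primary sample size, and it reproduces.
- Case coverage: 0.9×0.2/(0.1+0.9×0.2) = 0.643.
- Variance numerator: 1/(0.643×0.357) + 1/(2×0.9×0.1) = 9.91.
- A 95% interval 10 points wide around an odds ratio of 0.2 needs SE = arcsinh(0.10/0.40)/1.96 = 0.1263.
- n = 9.91/0.1263² ≈ 622 cases. Then 622/0.5×1.2 = 1,493, about 1,500.

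**Inputs from the article.** 2,034 participants were enrolled in the 13 weeks to 2 February 2022, or 156.5 per week. The remaining 4,500 − 2,034 = 2,466 are spread over 26 weeks, or 94.8 per week. Half qualify for the primary comparison. Coverage is about 2/3 at the start and 90% is planned among controls.

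**Assumptions, because the article gives none.**
- Omicron cases begin about week 8 (day 53 in a second calculation).
- Control coverage in week w is 0.90 − (0.90 − c0)·exp(−w/τ), with τ = 6 weeks (fast) or 15 weeks (slow). With c0 = 0.67, coverage at week 8 is 0.90 − 0.23×0.264 = 0.84 (fast) or 0.90 − 0.23×0.587 = 0.77 (slow).
- The 50% start is a scenario. If 2/3 were fully vaccinated and half of those had BNT162b2 (*Study setting*), then 1/3 had BNT162b2. Set against 1/3 unvaccinated, coverage in the primary comparison is 50%. It is higher if many of the remainder were partly vaccinated.
- Weekly positivity is either constant or wave-shaped (12%, then 60%, 15% and 40%).
- Case coverage is p·OR/(1 − p + p·OR), with OR = 1 − VE, constant over time.

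In the wave-shaped layout about 8 × (156.5×0.5) × 0.88 ≈ 550 of some 1,560 controls (35%) predate Omicron.

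**All controls, day count taken as linear.** Ranges span the positivity patterns and onset dates tried.

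| Coverage among controls | Estimate, true VE 50% | Estimate, true VE 0% |
|---|---|---|
| 67% to 90%, steady rise | 50% | 0% |
| 90% throughout | 50% | 0% |
| 67% to 90%, slow levelling | 47 to 48% | about −4 to −5% |
| 67% to 90%, fast levelling | 42 to 43% | about −14 to −20% |
| 50% to 90%, fast levelling | 37 to 40% | about −21 to −29% |

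At true VE 50% the odds ratio is inflated by 0.52–0.53/0.50 = 1.04–1.06 (slow), 0.57–0.58/0.50 = 1.14–1.16 (fast) and 0.60–0.63/0.50 = 1.20–1.26 (50% start).

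A wider grid of coverage shapes, onset days (45 or 60), control intake and Omicron wave shapes gave the following whenever coverage levelled off: 22.8 to 48.2% for true 50%, and 68.7 to 79.2% for true 80%. The low ends come from the most abrupt combination. With a linear rise the same grid gave 49.8 to 50.6% and 79.8 to 80.4%.

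**All controls, only the time term changed** (true VE 50%, 67% to 90%, fast): linear 41.8, quadratic 45.5, quartic 49.8, calendar-month categories 50.0. From the 50% start: linear 37.3, quartic 49.6, months 50.1. With month categories, a month with no Omicron cases carries no information on the vaccine odds ratio, so its controls drop out by themselves.

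**Controls restricted to the Omicron period, linear time kept:** 50 to 54% for true 50% in the enrolment-based scenarios, and 46.5 to 50.4% across the wider grid. Restriction with a straight line is close but not exact.

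**Delta, all controls, linear time:** 79.5 to 80.7% for true 80%.

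**The case against.** The strongest reply is that the reused model already adjusts for sampling date and that the article never says the adjustment is linear. Functional form is a detail an article may leave to a fuller plan, and a flexible form removes the bias with every control kept. Even a straight line does no harm if coverage rose steadily. The size rests on curves and dates the article does not contain. The 2/3 (target population, full vaccination) and the 90% (planning value among controls) have different denominators. In the slow-rise case the shortfall of 2 to 3 points is small beside an approximate 95% interval of 35 to 58%. *Overall principles* also labels secondary analyses exploratory.

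Most of this stands, and it limits the point. A reader might infer that the unrestricted control set alone biases Omicron VE, as a fault of control eligibility separate from how time is coded. The documents do not support that: with the same controls and month categories the bias disappears. A reader might also take the linear form as the plan's stated choice, which it is not.

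What remains is that the article does fix the approach for the variant analyses: the primary model, with one day-count covariate and no control window. A term that is adequate for all-variant infection need not be adequate for an outcome that cannot occur in the first weeks. A steady rise is also not the obvious reading of the article's figures, since a linear climb from 67% to 90% averages only about 77% among controls on the stated enrolment, against the planned 90%. That leans towards an early rise but does not settle it.

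**Conclusion.** The point holds conditionally. The problem is the combination of controls from all weeks with a single day-count term. If that term is linear and coverage rose early and then plateaued, Omicron VE is biased downward. For a true VE of 50% the shortfall is about 2 to 3 points (slow rise from 67%), 7 to 8 points (fast rise) or 10 to 13 points (assumed 50% start). It is about zero with steadily rising or flat coverage, and about zero with flexible time. Delta VE is little affected.

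These sizes depend on assumed coverage curves, positivity and Omicron onset, and on a time-constant odds ratio. The primary analysis and the sample size are not touched. This is a cheap and worthwhile improvement to a secondary analysis, not evidence that the planned Omicron estimate must be wrong.

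**What to change.** Add a sentence to *Secondary outcome analyses*. For each variant-specific VE, choose one of two approaches as the main analysis and report the other as a sensitivity analysis:

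- limit both cases and controls to the calendar period in which that variant was identified among the study's own genotyped cases, with time adjustment inside that period, preferably flexible; or
- keep all controls and model calendar time flexibly, with a spline or with calendar-week or calendar-month categories.

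All positive samples are screened for variants and sample dates are already in the model, so nothing new is collected. Restriction leaves fewer controls (about 1,000 instead of 1,560 for Omicron and about 575 for Delta in the scenario above). Flexible time costs a few degrees of freedom. Either way the intervals widen slightly.
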